## Abstract

**Introduction:**

Sarcopenic obesity (SO) is characterised by decreased muscle mass, diminished muscle strength and/or reduced physical performance and a high percentage of body fat (PBF). Conventional-load resistance exercise (CRE) may be difficult for older people with SO owing to their declining physical functions. Low-load resistance exercise (LRE) combined with blood flow restriction (BFR; LRE-BFR) is a viable alternative to CRE for improving muscle mass and strength and potential exercise mode for managing SO. This study has two objectives: (1) to comprehensively evaluate the efficacy of CRE and LRE-BFR in improving body composition, muscle strength, physical performance, haematological parameters, cardiovascular disease (CVD) risk factors and quality of life and (2) to compare the efficacy of CRE and LRE-BFR and explore their potential mechanisms.

**Methods and analysis:**

This work is a 12-week assessor-blinded randomised clinical trial that will be conducted thrice a week. Sarcopenia will be defined using the Asian Working Group for Sarcopenia 2019, and obesity will be determined using the criteria developed by the World Health Organization. Community-dwelling older people aged ≥ 65 years will be screened as the participants using inclusion and exclusion criteria. A total of 33 participants will be randomised into a CRE group (*n* = 11), an LRE-BFR group (*n* = 11) and a control group that will be given only health education (*n* = 11). The primary outcomes will be knee extensor strength and PBF, and the secondary outcomes will be body composition, anthropometric measurements, muscle strength of upper limbs, physical performance, haematological parameters, CVD risk factors and quality of life. The outcomes will be measured at the baseline (week 0), end of the intervention (week 12) and follow up (week 24). All the collected data will be analysed following the intention-to-treat principle.

**Ethics and dissemination:**

The Ethics Research Committee has approved this study (approval No. CMEC-2022-KT-51). Changes or developments in this study will be reported at www.chictr.org.cn.

**Trial registration:**

ChiCTR2300067296 (3 January 2023).

**Supplementary Information:**

The online version contains supplementary material available at 10.1186/s12877-023-04592-9.

## Introduction

The accompanying features of sarcopenia and obesity include sarcopenic obesity (SO), which is characterised by decreased skeletal muscle mass, diminished muscle strength and/or reduced physical performance and a high percentage of body fat (PBF) [1]. A meta-analysis of 50 studies showed that the global prevalence of SO was 11% in December 2020, meaning that more than 1 in 10 older people demonstrated adverse health outcomes globally [2]. Several studies reported that SO may result in a two- to threefold higher risk of functional disability [3] as well as hypertension [4], hyperglycaemia [4], dyslipidaemia [5], type 2 diabetes [6] and insulin resistance (IR) [5] compared with sarcopenia alone or obesity alone. The rise in cardiovascular disease (CVD) risk factors has been identified as one of the most important public health problems in the world [7], and CVD is the leading cause of death worldwide [8]. Stephen et al. [9] indicated that older people with SO have an increased risk of CVD by 23% compared with those without SO. The negative health outcomes of older people with SO indicate that early identification and effective intervention are necessary to improve their quality of life.

The pathogenesis of SO is multifactorial. The common pathophysiological basis of sarcopenia and obesity may play a synergistic role in the progression of SO, including increased inflammatory factors (e.g. interleukin 6 [IL-6], C-reactive protein [CRP] and tumour necrosis factor-α [TNF-α]), IR (e.g. serum insulin), endocrine dysfunction (e.g. insulin-like growth factor 1 [IGF-1], leptin [LEP] and adiponectin [ADP]), changes in myostatin (MSTN) and decreased physical activity (PA) [10–12]. In the absence of specific pharmacological treatment, PA is considered to be an effective strategy for managing SO [13, 14].

Specific PA guidelines for older people with SO are lacking. Conventional-load resistance exercise (CRE) is essential for increasing muscle mass and strength and improving physical performance and plays a positive role in reducing PBF and thus may be a promising strategy for managing SO [15–17]. Unfortunately, studies on the efficacy of CRE in managing SO are limited. To increase muscle mass and muscle strength, the American College of Sports Medicine (ACSM) recommends an exercise load of 60%–80% of one-repetition maximum (1RM) for older people [18]. However, this load may induce excessive stress on the joints and connective tissues of older people, which may increase their risk of injury [19]. CRE depends generally on gym machines, which are expensive and not portable, thereby making them unsuitable for most community settings [20]. Therefore, finding an alternative to CRE that is cheap, portable and has a low risk of injury is essential to manage SO.

Blood flow restriction (BFR) is a technique that involves the use of a bandage to apply pressure to a proximal limb to block venous blood return and partially block arterial blood flow, thereby increasing the local metabolic pressure of the body [21, 22]. Lixandrão et al. [23] validated that the combination of low-load resistance exercise (LRE) with BFR (LRE-BFR) at 20%–30% of 1RM is a viable alternative to CRE for improving muscle mass and strength. Similarly, a recent systematic review and meta-analysis explored the effects of BFR on the older people and revealed that LRE-BFR has similar effects to CRE in terms of increased muscle strength and muscle mass [24]. Increased muscle mass has positive implications for obese individuals, such as body composition improvement and insulin sensitivity [25]. In an 18-week study, LRE-BFR was able to reduce the PBF, fasting plasma glucose (FPG) and fasting insulin (FINS) but increased ADP [25]. Research on the application of LRE-BFR in SO management is lacking, but LRE-BFR is beneficial to the musculoskeletal system and body composition of individuals with sarcopenia and those suffering from obesity. Thus, we speculate that LRE-BFR may be a potential exercise mode for older people with SO. However, little is known about the effects of LRE-BFR on the cardiovascular system, which suggests that physiological changes such as blood pressure and heart rate should be closely monitored when implementing interventions for older people with SO, who are at risk of CVD.

Therefore, this study has the following objectives: (1) to comprehensively evaluate the efficacy of a 12-week CRE and LRE-BFR intervention in improving the body composition, muscle strength, physical performance, haematological parameters, CVD risk factors and quality of life of older people with SO and (2) to compare the efficacy of CRE and LRE-BFR and explore their potential mechanisms.

## Methods and analysis

### Study design

This work is a 12-week assessor-blinded randomised clinical trial (RCT) that will be conducted thrice a week, with two intervention groups and one control group. This study was registered on the Chinese Clinical Trial Registry, with registration number ChiCTR2300067296. The experimental flow chart is shown in Fig. 1, and the intervention and assessment schedules are presented in Table 1. The 2013 Standard Protocol Items for Randomized Trials checklist [26] is available in Additional file 1.

**Fig. 1 Fig1:**
[figure not shown]
Flow chart showing the participant recruitment, intervention and assessment process. PBF: percentage of body fat; LRE-BFR: low-load resistance exercise with BFR; CRE: conventional-load resistance exercise

**Table 1 Tab1:** The timetable for participant recruitment, intervention, and assessment

Measurement	Before (week 0)	Baseline (week 0)	Intervention (week 1-week 12)	End of intervention (week 12)	Follow-up (week 24)
Enrollment					
Recruitment and screening	X				
Information consent	X				
Allocation		X			
LRE-BFR			X		
CRE			X		
CG			X		
Primary outcomes					
PBF		X		X	X
KES		X		X	X
Secondary outcomes					
Body composition		X		X	X
Anthropometric measurements		X		X	X
Muscle strength of upper limbs		X		X	X
Physical performance		X		X	X
Hematological parameters and CVD risk factors		X		X	X
Quality of life		X		X	X
Others					
Participants' compliance			X	X	X
Adverse events			X	X	X
Reasons for dropout			X	X	X

*LRE-BFR* Low-load resistance exercise with BFR, *CRE* Conventional-load resistance exercise, *CG* Control group, *PBF* Percentage of body fat, *KES* Knee extension strength, *CVD* Cardiovascular disease

### Study setting

Recruitment will be conducted in four communities in the Chongming District, Shanghai, China, from 1 October 2023 to 1 December 2023. According to the established inclusion and exclusion criteria, 33 participants will be screened for the group interventions. All the participants will be assessed at three time points: before the intervention (week 0), at the end of the intervention (week 12) and after the intervention (week 24).

### Inclusion criteria

1. Individuals aged ≥ 65 years.2. Individuals who meet the SO diagnostic criteria.

### Sarcopenia

Appendicular skeletal muscle mass index (ASMI) measured via bioelectrical impedance analysis (BIA): < 7.0 kg/m^2^ in men and < 5.7 kg/m^2^ in women; and handgrip strength (HS): < 28 kg in men and < 18 kg in women; and/or 6-m gait speed (GS) < 1 m/s (according to the Asian Working Group for Sarcopenia [AWGS] 2019) [27]

### Obesity

PBF ≥ 35% for women and ≥ 25% for men (World Health Organization [WHO] criteria) [28]3. Individuals with no regular exercise habit (do not engage in PA at least 3 days/week, 30 min/day, of moderate intensity, for at least 3 months) [29]4. Voluntary participation and a signed informed consent form.

### Exclusion criteria

1. Individuals with absolute contraindications to exercise, such as deep vein thrombosis and/or coagulation disorders2. Individuals with a cognitive impairment, hearing impairment or visual impairment that will prevent normal communication with the researchers; cognitive impairment will be assessed using the Mini-Mental State Examination [30], with the score interpreted according to the participant’s literacy level; a score of ≤ 17 for illiterates, ≤ 20 for elementary school graduates and ≤ 24 for middle school graduates indicates cognitive dysfunction.3. Individuals that will experience difficulty completing the assessment and/or exercise interventions, such as those with a musculoskeletal disorder (e.g. fracture and/or dislocation), CVD (uncontrolled hypertension with systolic blood pressure [SBP] > 200 mmHg or diastolic blood pressure [DBP] > 110 mmHg, uncontrolled dyslipidaemia with total cholesterol [TC] > 220 mg/dl, history of stroke, acute myocardial infarction, angina pectoris and uncontrolled ventricular tachycardia) or disability (e.g. loss of hands or feet).4. Individuals with an infectious skin disease and/or unhealed and/or festering wounds5. Individuals who have been taking the following medications regularly for the past 3 months: antiplatelet medications (e.g. aspirin, cilostazol, Aggrenox, cilostazol, ticlopidine, eptifibatide and tirofiban), analgesic medications and anticoagulant medications.

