### Screening

The participants will be determined through two steps.

Step 1: All the recruited older people will be screened using the SARC-F questionnaire and PBF. Only those who obtain a SARC-F questionnaire score of ≥ 4 and with a PBF of ≥ 35% (women) or ≥ 25% (men) will proceed to the second step.

The SARC-F questionnaire includes five components: strength, assisted walking, rising from a chair, stair climbing and falling [31]. The questionnaire has a total score ranging from 0 (best) to 10 (worst), and a total score of ≥ 4 is considered to be at risk of sarcopenia [27].

Step 2: The final participants of the study will be assessed further using the inclusion and exclusion criteria.

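### The exclusion criteria name deep vein thrombosis but not arterial disease of the legs, although the LRE-BFR cuff partly blocks arterial flow in both legs

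*Protocol article*

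**What the plan says.** The Exclusion criteria section has five items. Four bear on this point.

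- Criterion 1: "Individuals with absolute contraindications to exercise, such as deep vein thrombosis and/or coagulation disorders".
- Criterion 3: "Individuals that will experience difficulty completing the assessment and/or exercise interventions, such as those with a musculoskeletal disorder". It also covers cardiovascular disease, with a bracketed list: hypertension and dyslipidaemia above stated limits, then "history of stroke, acute myocardial infarction, angina pectoris and uncontrolled ventricular tachycardia".
- Criterion 4: "Individuals with an infectious skin disease and/or unhealed and/or festering wounds".
- Criterion 5: "Individuals who have been taking the following medications regularly for the past 3 months: antiplatelet medications". Analgesics and anticoagulants are covered too.

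The Introduction describes the action of the cuff: it is there "to block venous blood return and partially block arterial blood flow". The LRE-BFR section places cuffs at the top of both legs at 50% of individual LOP, continuously inflated, with the condition that they cause no discomfort. Training is three times a week for 12 weeks.

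LOP is found with a Doppler probe over the tibial artery before training begins. The Group protocols section confines this test to the LRE-BFR group.

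Screening Step 1 uses SARC-F and body fat. Of Step 2 the protocol says: "The final participants of the study will be assessed further using the inclusion and exclusion criteria".

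**The concern.** The list already screens for several hazards relevant to a cuff: thrombosis, coagulation disorders, skin disease and wounds, and antithrombotic drugs. It does not name disease of the leg arteries, although the protocol itself says the cuff reduces flow in those arteries.

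The people recruited are 65 or older with sarcopenic obesity, which the Introduction links to hypertension, dyslipidaemia, diabetes and higher cardiovascular risk. The Discussion says that evidence on the cardiovascular safety of LRE-BFR is lacking, particularly for older people with such risk factors.

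What is at stake is whether a person already known to have impaired arterial supply to the legs can be allocated to repeated restriction of that supply. No outcome, estimate or test in the plan is affected.

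**Working it through.** There is no statistical figure to reproduce. The check reads the criteria against the intervention, followed by simple exposure arithmetic.

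**Step 1. What each criterion would catch**

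| Criterion | Reaches leg arterial disease? |
|---|---|
| 1 | Open-ended, but only towards absolute contraindications to exercise. Cuff restriction is not the test. |
| 3, general clause | Open-ended, but the test is difficulty completing the assessments or the exercise. |
| 3, cardiovascular list | Six conditions: hypertension, dyslipidaemia, stroke, myocardial infarction, angina, ventricular tachycardia. None is in the leg vessels. |
| 4 | Catches ulcerated cases only. |
| 5 | Catches people on regular antiplatelet, anticoagulant or analgesic drugs. |

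**Step 2. Would the difficulty test in criterion 3 exclude the rest?** Not reliably. The training movements are bicep bends, seated rows and seated knee extensions. The walking assessments cover 6 m and 4 m. A person whose leg arteries limit longer walking could complete all of these.

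**Step 3. Who remains.** A person with known leg arterial disease who can do the seated exercise and the short tests, has no wound and takes no listed drug. Nothing written requires that this person be excluded.

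**Step 4. Is there a later check?** The Doppler examination comes before training but only in the LRE-BFR group, so it follows allocation. The text states no consequence of an abnormal finding, or of a pressure that cannot be obtained.

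**Step 5. Planned exposure for one person in the cuff arm**

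- Sessions: 3 per week × 12 weeks = 36.
- Cuffed time if the cuff is inflated only for the 20-minute exercise block: 36 × 20 = 720 min = 12 h.
- Cuffed time if it is inflated for the whole 30-minute session: 36 × 30 = 1,080 min = 18 h.
- Chance of the cuff arm under 1:1:1 allocation: 11/33 = 1/3.

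The sessions and hours are the planned dose for anyone in that arm. They do not measure added risk.

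**The case against.** **The list is open, not closed.** Criteria 1 and 3 give examples, and LRE-BFR is itself one of the exercise interventions that criterion 3 refers to. An investigator could hold that a person with poor leg circulation would have difficulty completing cuffed exercise. This stands as a route to exclusion by discretion. It does not make exclusion a rule: the test is ability to complete, not hazard from the cuff, and nobody has been cuffed when eligibility is judged.

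**The added risk is not documented.** The article does not say that leg arterial disease is a contraindication at 50% LOP, and the BFR guidelines it cites are not available here. This stands. The risk is inferred from the mechanism in the Introduction.

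**Safeguards exist before and during training.** Pressure is set from each person's own LOP before the programme and must cause no discomfort. There are three familiarisation sessions, supervised exercise, reporting of adverse effects to the ethics committee, a Data Monitoring Committee, and fatigue monitoring with adjustment of the prescription. For safety, a check before exposure matters more than a check before allocation, and the Doppler test comes before exposure. This is fair and lowers the severity. But the Doppler test is described only as a way to set pressure, and none of the other safeguards asks about known disease.

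**Stronger readings that a reader might infer.** One is that leg venous disease short of thrombosis, such as varicose veins or chronic venous insufficiency, is an equal omission. The protocol does say venous return is blocked, but nothing in it indicates who would be harmed by that, and the case is open to debate. Another is that affected participants are likely to be present in the arm of 11. Any such probability needs a prevalence, which the document does not give.

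**Conclusion.** The point holds as a narrow eligibility gap. Leg arterial disease is not named, the cuff acts on leg arteries, and the remaining criteria do not require exclusion of a person with known disease who can exercise seated, has no wound and takes no listed drug. Making that exclusion explicit is a cheap improvement to patient safety.

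Its size cannot be given as a count. The document supplies neither the prevalence of such disease nor its risk under the cuff, and after criteria 3 to 5 the group is probably small. What can be stated is the exposure such a person would face: a 1 in 3 chance of 36 planned cuffed sessions, or 12 to 18 hours. Multiplying this up to a whole-arm total would describe the trial's workload, not anyone at added risk.

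The conclusion rests on two assumptions: that restricted arterial inflow is less safe where inflow is already impaired, and that investigators apply the criteria as written. The text does not support a reading that vascular safety was ignored, that anyone is expected to be harmed, or that the trial's results would be biased.

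**What to change.** Add one line to the Exclusion criteria: known or symptomatic peripheral arterial disease of the legs. Apply it to every candidate, whichever group they may later join, by a few history questions and a simple look at the legs at the existing Step 2, before allocation. Naming known significant leg venous disease as well is optional and can be left to the investigator's clinical judgement. A further optional clarification is to state what happens if LOP cannot be obtained in a participant already allocated to LRE-BFR.

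The cost is a few minutes per candidate, slightly more screen failures to absorb in a recruitment window running "from 1 October 2023 to 1 December 2023", and a slightly narrower population. History and inspection will largely miss silent disease, which may still first appear at LOP testing.

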### Termination criteria

1. Individuals who will withdraw from the study at any time.2. Individuals who will experience serious adverse effects during or after the exercises and will be unable to continue their participation.3. Individuals who will lose contact during the exercise interventions and/or follow-up period.

### Recruitment

The participants will be recruited through the following four ways:1. During annual physical examinations in four communities in the Chongming District, Shanghai, China.2. During educational lectures on SO that will be conducted in four communities in the Chongming District to attract potential participants.3. During home visits to older people who do not participate regularly in their annual physical examination, in cooperation with community workers.4. The research proposal posted on the community bulletin board.

### Screening

The participants will be determined through two steps.

Step 1: All the recruited older people will be screened using the SARC-F questionnaire and PBF. Only those who obtain a SARC-F questionnaire score of ≥ 4 and with a PBF of ≥ 35% (women) or ≥ 25% (men) will proceed to the second step.

The SARC-F questionnaire includes five components: strength, assisted walking, rising from a chair, stair climbing and falling [31]. The questionnaire has a total score ranging from 0 (best) to 10 (worst), and a total score of ≥ 4 is considered to be at risk of sarcopenia [27].

Step 2: The final participants of the study will be assessed further using the inclusion and exclusion criteria.

### Randomisation and blinding

The final participants will be randomly assigned to an LRE-BFR, CRE or control group, with a 1:1:1 ratio. To ensure the allocation concealment, the randomisation sequence will be generated after the baseline assessment by a statistician who is not involved in the study, using SPSS version 26 (SPSS, Inc., USA), and stratified by gender and age to achieve a balanced distribution, with as many males and females in each group as possible. An electronic file of the random numbers and grouping will be encrypted by the statistician and sent to another external researcher to store the information. The information will be given to the therapist in a sealed envelope. All the outcome assessors, statisticians and data managers involved in this study will be blinded to the group assignment prior to the completion of the statistical analysis. Given the nature of this study, the participants and therapist cannot be blinded to the group assignment.

### Interventions

#### Group protocols

Before the formal interventions, the participants in the LRE-BFR and CRE groups will undergo 1RM testing and be taught how to use the Borg rating of perceived exertion (RPE) scale ranging from 6 to 20 to determine the target resistance load, and the RPE scores during the intervention will be recorded. The exercise intensity will be set based on the TheraBand force–elongation table to select the appropriate elastic band, which is reflected in the elastic band colour, from yellow to red to green. Limb occlusion pressure (LOP) testing will be performed in the LRE-BFR group. The participants’ attendance and occurrence of any adverse effects during the exercise interventions and follow-up period will be recorded by a dedicated investigator. If a participant misses a planned exercise intervention, they will make up the session at another time during the same week. All the participants will have three preintervention sessions to familiarise themselves with the exercise flow. The intervention protocols for the three groups are presented in Table 2.

**Table 2 Tab2:** Details of the three groups of protocol

Weeks	Group	Specific intervention content	Sets	Repetitions	Interval rest time between sets (s)	Intensity	Frequency (times/week)
1–4	LRE-BFR	Biceps bend, seated row, seated knee extension	4	30,15,15,15	30	20% 1RM	3
	CRE					60% 1RM	
	CG	Education session (no intervention)	/	/	/	/	1
5–8	LRE-BFR	Biceps bend, seated row, seated knee extension	4	30,15,15,15	45	25% 1RM	3
	CRE					65% 1RM	
	CG	Education session (no intervention)	/	/	/	/	1
8–12	LRE-BFR	Biceps bend, seated row, seated knee extension	4	30,15,15,15	60	30% 1RM	3
	CRE					70% 1RM	
	CG	Education session (no intervention)	/	/	/	/	1

*LRE-BFR* Low-load resistance exercise with BFR, *CRE* Conventional-load resistance exercise, *CG* Control group, *1RM* One-repetition maximum

